### The treatment period (Interview 4, 4 weeks ± 3 days)

After the subjects taking 4 weeks the research drugs in the double-blind randomized treatment period, the following aspects should be done:

- - Resting sitting blood pressure and heart rate were measured: the measurement method is the same as that of the screening period;
  - Laboratory examinations: urine routine test test, liver function, renal function and serum electrolyte;
  - According to the distributed random numbers, the research drugs for the fifth ~ eighth week treatment period were given (including 6 days of alternative drug);
  - Recovery and counting of the third ~ fourth week remaining reserch drugs;
  - Transfer and recording of the diary cards of subjects;
  - Recording adverse events and concomitant treatments.

### Finishing of the random therapy (Interview 5, 8 weeks ± 3 days)

After the subjects taking 8 weeks of the research drugs in the double-blind randomized treatment period, the following aspects are needed:

- - Physical examinations: physical examination of all body systems including weight;
  - Resting sitting blood pressure and heart rate were measured: the measurement method was as the same as that of the screening period;
  - Laboratory and auxiliary examinations: including urine pregnancy test (limited to women of childbearing age), whole blood test, urine routine test test, liver function, renal function, fasting blood glucose, blood lipid, blood electrolyte and 12-lead electrocardiogram.
  - Recovery of the fifth ~ eighth week remaining study drug and counting;
  - Distribution of Allisartan Isoproxil tablets for 9-weeks doses;
  - Recovery, transfer and recording of the diary cards of subjects;
  - Recording adverse events and concomitant treatments.

### The safety observation period (Interview 6-11, 9-56 weeks, every interview for 8 weeks, the window period ± 7 days)

In order to observe the long-term efficacy and safety of the research drugs, all the subjects would participate in the safety observation period research of 56 weeks voluntarily after they finish the double-blind randomized study of 8 weeks, during which each subject will receive 240 mg Allisartan Isoproxil tablet treatment once a day, and the subjects should visit the doctor every 8 weeks:

- - Resting sitting blood pressure and heart rate were measured: the measurement method is the same as that of the screening period;
  - Laboratory examinations: urine routine test test, liver function, renal function and serum electrolyte (if the laboratory indicators are abnormal in the observation of former 8 weeks, please reexamine; if it is normal, please judge freely whether reexamination is necessary according to the circumstances);
  - Distribution of Allisartan Isoproxil tablets for 9 weeks doses;
  - Residual drug recovery of the past 8 weeks and counting;
  - Recovery, transfer and recording of the diary cards of the subjects;
  - Recording adverse events and concomitant treatments.

The interview 9, namely the interview of the subjects taking the research drugs for 32 weeks during the safety observation period, in addition to the above items, the following aspects are also needed to be conducted:

- - Physical examination: physical examination of all body systems including weight;
  - Laboratory examinations: urine routine test test, liver function, renal function and serum electrolyte;
  - Laboratory and auxiliary examinations including whole blood test, fasting blood glucose, blood lipid, blood electrolyte and a 12-lead electrocardiogram.

### The finishing of the safety observation period (Interview 12, the sixty-fourth week ± 7 days)

After the participants complete the observation period of 56 weeks of treatment, the following aspects are needed:

- - Physical examination: physical examination of all body systems including weight;
  - Resting sitting blood pressure and heart rate were measured: the measurement method is as the same as that of the screening period;
  - Laboratory and auxiliary examinations: including urine pregnancy test (limited to women of childbearing age), whole blood test, urine routine test test, liver function, kidney function, fasting blood glucose, blood lipid, blood electrolyte and a 12-lead electrocardiogram.
  - Recovery of the fifty-seventh ~ 64th week remaining study drug and counting;
  - Recovery and transfer and recording of diary cards of the subjects;
  - Recording adverse events and concomitant treatments.

### The unplanned outside interview

If subjects need extra interviews or early exiting test, the measures having been taken by researchers (including laboratory test results) should be recorded on the original case history and the unplanned interview table in the case report table.

In addition, when the subjects exit the tests early before the interview 5 or enter the safety observation period early to end the safety observation period, the following aspects should be done as far as possible:

- - Physical examination: physical examination of all body systems;
  - Resting sitting blood pressure and heart rate were measured: the measurement method is as the same as that of the screening period;
  - Laboratory and auxiliary examination: including urine pregnancy test (limited to women of childbearing age), whole blood test, urine routine test test, liver function, renal function, fasting blood glucose, blood lipid, blood electrolyte and a 12-lead electrocardiogram;
  - Recovery of all the remaining study drug and counting;
  - Recovery, transcfer and recording of the diary cards of the subjects (only applicable to the subjects during the double-blind study);
  - Recording adverse events and concomitant treatments.

# Research drugs

## Drug name, dosage form

Test drug: Allisartan Isoproxil tablet (ALS-3), specification of 80mg/tablet (each tablet containing 80mg ALS-3), produced and provided by Shenzhen Salubris Pharmaceuticals Co.,Ltd

and the Shanghai ALLIST medicine technology limited, batch number: 20090301.

Placebo: Allisartan Isoproxil placebo tablet, specifications 80mg/tablet, produced and provided by Shenzhen Salubris Pharmaceuticals Co.,Ltd and the Shanghai ALLIST medicine technology limited, batch number: 20090303.

## Medication methods

**The double-blind treatment period**

Test group: Allisartan Isoproxil tablet 240 mg, 1 time a day, oral administration of half an hour before breakfast fasting for 8 weeks.

Control group: Allisartan Isoproxil placebo tablet 240mg, 1 time a day, oral administration of half an hour before breakfast fasting for 8 weeks.

**Safety observation period**

Allisartan Isoproxil tablet 240 mg, 1 time a day, oral administration of half an hour before breakfast fasting for 56 weeks.

## Storage conditions

Below 30℃, dry places for preservation.

## Drug packaging and labeling

### Packaging of drugs in wash-out period

Two weeks cleaning period of research drug is 1 independent packaging. In order to ensure that the subjects are blinded, the packaging is not indicated the cleaning period of drugs and labeled as "Allisartan Isoproxil clinical trial drug (the first – the second week)". Only the screening number is filled but not the drug number. Drug packaging: Allisartan Isoproxil placebo 80mg/tablet; each plate contains 3 Allisartan Isoproxil placebo, and a total of 17 plates are included (including 3 days alternative drugs); fasting oral administration half an hour before breakfast, 1 time a day, each time for 1 plate.

### Packaging of drugs during the treatment period

The packaging of the research drugs include large packaging, big packaging, middle packaging and small packaging.

Each of the large package (big bog) includes the research drugs for 8 weeks randomized double-blind treatment period on a subject, which is labeled as "Allisartan Isoproxil clinical trial drug (the third – the tenth week), containing 4 large packages (a total of 68 plates).

Each of the large package (small bag) includes the research drugs for 2 weeks of the treatment period on a subject, which is labeled as "Allisartan Isoproxil clinical trial drug (the x – the x week), containing 3 middle packages (a total of 17 plates).

The middle packag (Aluminium plastic composite film bags) is divided into two kinds: one is "7 days of medication" (a total of 7 plates) and another is a "3 days of alternative medicine" (a total of 3 plates).

Each small packag is 1 aluminum plate. Each plate contains Allisartan Isoproxil tablet/placebo of 3 tablets, which is 1 day of medication.

### Labels of the research drugs

The labels of the research drugs include the labels of the research drugs in the cleaning period, the research drug of the randomised double-blind treatment period and the research drug of the safety observation period (Appendix 3).

## Drug distribution and checking

The cleaning period drugs for 2 weeks were distributed by the research physician in charge of Drug Administration to the preliminarily screened eligible subjects, which was recorded. After finishing the cleaning period for 2 weeks, the physicians were responsible for the recovery and counting the residual drugs and empty packaging inventory of the selected subjects.

After the cleaning period, the included subjects were further screened for the qualified subjects according to the research protocol. According to the selected sequence from small to large, random numbers (i.e. drug number) were distributed, and 1 ~ 2 weeks of the research drugs corresponding to the drug number in the randomized double-blind treatment period were distributed. The amount of the distributed drugs was recorded.

After finishing the treatment for 2 weeks, the subjects were interviewed by returning to the research center according to the research protocol. The research physician were responsible for the recovery and counting of the remaining drug number and empty package of all subjects, and 3-4 weeks randomized double-blind research drugs in the treatment period were distributed. The number of recovery and distributed drugs were recorded.

After finishing the treatment for 4 weeks, the subjects were interviewed by returning to the research center according to the research protocol. The research physician were responsible for the recovery and counting of the remaining drug number and empty package of all subjects, and the fifth to the eighth week randomized double-blind research drugs in the treatment period were distributed. The number of recovery and distributed drugs were recorded.

After finishing the treatment for 8 weeks, the subjects were interviewed by returning to the research center according to the research protocol. The research physician were responsible for the recovery and counting of the remaining drug number and empty package of all subjects, and the ninth to the sixteenth week randomized double-blind research drugs in the treatment period were distributed. The number of recovery and distributed drugs were recorded.

In the 56 weeks of safety observation period, the subjects were interviewed by returning to the research center according to the research protocol. The research physician were responsible for the recovery and counting of the remaining drug number and empty package of all subjects, and the ninth to the sixteenth week randomized double-blind research drugs in the treatment period were distributed. The number of recovery and distributed drugs were recorded.

After finishing the 56 weeks of safety observation period, the subjects were interviewed by returning to the research center according to the research protocol. The research physician were responsible for the recovery and counting of the remaining drug number and empty package of all subjects.

Whether the subjects complete the study or not, the untaken drugs and empty packaging must be returned to the researchers. Researchers should keep all the returned drugs and empty packaging for the recording until the CRO company together recovery of the not distributed products.

## The principle of dose selection and dose adjustment

**The selection principle of the doses of the research drugs and dosage adjustment:**

The reserch dose of the present clinical trial is set as 240mg, mainly taking the following factors into consideration:

In the already finished phase II clinical study of Allisartan Isoproxil, from the angle of the pressure amplitude and standard rate, the antihypertensive efficacy of the Allisartan Isoproxil tablets of 80mg, 160mg and 240mg was comparable to that of the 50mg losartan potassium, of which the antihypertensive effect of the Allisartan Isoproxil in the 240 mg group was similar to that fo the 50 mg losartan potassium, and the antihypertensive consistency in different treatment times was good, and the fluctuation was small. In security, there was no significant difference in the adverse events, adverse reactions and laboratory tests, vital signs and physical examinations between the groups of Allisartan Isoproxil with doses of 80mg, 160mg and 240mg and the group of losartan potassium with 50mg. However, of the 3 doses of Allisartan Isoproxil, the group of 240 mg Allisartan Isoproxil tended to show stronger roles in reducing blood lipid and renal protective effect. And in the indexes of liver function, there was no significant difference before and after treatment and between different groups. In the aspects of comprehensive efficacy and safety performance, this study chooses the 240mg dose as the test dose.

Throughout the study, the dose remained unchanged and there is no dose adjustment.

# Treatment of subjects

## Research drugs

All the preliminarily screened qualified patients intending to participate in the study, they all take the research drugs in the 2 weeks cleaning period :

Placebo: Allisartan Isoproxil placebo tablet: 80mg, 3 tablets.

After the 2 weeks cleaning period, 260 subjects meeting grouping conditions were randomly assigned to the following one of the two groups:

- Test group A: Allisartan Isoproxil tablet 240mg (Allisartan Isoproxil tablets 80mg, 3 tablets), once a day, fasting oral administration half an hour before breakfast;
- Placebo group B: Allisartan Isoproxil placebo tablet 240mg (Allisartan Isoproxil placebo tablets 80mg, 3 tablets), once a day, fasting oral administration half an hour before breakfast;

All the subjects finished the double-blind randomized studies after 8 weeks of treatment. All subjects participated in the safety observation research with a period of 56 weeks on a voluntary basis, during which, the participants took Allisartan Isoproxil tablets 240mg (Allisartan Isoproxil tablets 80mg, 3 tablets), once a day, fasting oral administration half an hour before breakfast.

## Combined application of drugs

Combined application of Losartan potassium with potassium supplement pills or isokalaemic diuretic (such as spironolactone, triamterene, amiloride etc.) may cause the increase in serum potassium level. Losartan potassium can increase the toxicity of lithium. Fluconazole can inhibit the transformation of losartan potassium into active metabolites of EXP3174. Similar to other anti hypertensive drugs, the non-steroidal anti-inflammatory drug indometacin can decrease the antihypertensive effects of losartan potassium. Rifampicin had obvious induction roles to the present drug and its metabolites EXP3174, reducing AUC and serum concentration of the drug and decreasing its efficacy. Ephedra contains ephedrine and pseudoephedrine, which can reduce the antihypertensive effects of the drugs. For the patients with hypertension treated with losartan potassium, formulations containing ephedra should be avoided.

EXP3174 is the active medicinal product of ALS-3. The active metabolites of losartan potassium playing main pharmacodynamic actions are also EXP3174. The matters needing attention in the specification of losartan potassium have very important reference value to ALS-3. Therefore, the above drugs refered to are not allowed to be used in the study period (including the cleaning period of 2 weeks), and any other drugs for treating hypertension are prohibited at the same time.

The interaction of drugs in the clinical application of Allisartan Isoproxil that may happen has not been studied.

All the concomitant medications were recorded in the corresponding position of the case report form.

## Subjects compliances

For the compliances of the medication orders, the drug use situation was calculated according to the recovery quantity of the distributed drugs combined with the diary cards of the subjects;

Actual dose of drug taken by subjects

Compliance＝

The dose of drug should be taken by the subjects

If the compliance of subject  80％, or  120％, indicating that the compliance is poor, not entering the per protocol set for analysis.

# Efficacy assessment

## Primary outcome

- The changes from baseline in trough mean seated DBP (23 to 26 hours after the morning dose) to the end of the 8-week double-blind treatment period.

Baseline refers to the sitting blood pressure before giving the research drug in the randomized double-blind treatment period and after 2 weeks cleaning period.

## Secondary outcome

- The change of trough mean seated DBP after 4 weeks treatment
- The change of trough mean seated SBP after 4 ,8weeks treatment
- Effective rate after 4,8 weeks treatment
- The change of trough mean seated SBP/DBP after 4, 8weeks treatment in effective patient.

Note: Effective respond was defined as the seated SBP/DBP<140/85mmHg, or seated SBP decrease≥20mmHg and/or seated DBP≥10mmHg.

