| **Statistical analysis** | **Estimation of sample sizes:**  This is a superior efficacy test study. The efficiency test was conducted on the main therapeutic effect index. Setting bilateral α = 0.05, *β* = 0.20, and the standard deviation SD = 7.8 mmHg, the difference of the antihypertensive effect in the two groups were detected as *D* = 3 mmHg. The distribution ratio of the patient cases in the two groups was 1:1. The estimated minimum sample size was 108 pairs. Taking into account of the factors such as dropping, the present research plan included 260 cases into the two groups with 130 cases of patients in the experiment group and the control group, respectively.  **Statistical analysis of the data set:**  Statistical analysis was conducted by using the full analysis set, per-protocol population set and safety data set. The quality control was strictly carried out in the whole process of the data statistics to ensure the authenticity of the assessment of data.  Full analysis set (Full analysis set, FAS): according to the fundamental principle of intention to treat (ITT), all the randomly enrolled subjects with more than one medication administration record and effective evaluation were included in the full analysis set. When selecting full analysis set for analysis, the latest observation LOCF (LOCF) estimation method was adopted for the estimation of the missing values. Full analysis set is the main effectiveness method for the evaluation of population in the present study.  The Per-Protocol set (PPS): PPS included all the subjects with completed prescribed treatment protocal or no serious violations of tests. The exact definition of the serious violations of the scheme will ultimately determined in the data auditing, which generally included the following situations (but they are not limited to these cases): Not meeting the inclusion criteria, having interference treatment after being selected, poor compliance, interview beyond the time window. PP set is a secondary analysis of the crowds of the effectiveness, but if the results were inconsistent with the full analysis set, detailed analysis should be done on the inconsistent results.  Safety data set (Safety Set, SS): the definition of safety data set was the subjects that at least received one time drug treatment.  **Statistical analysis method:**  Statistical analysis was conducted by using the SAS9.13 statistical analysis software for calculation. Quantitative description of the parameters included the calculation of mean, standard deviation, median, minimum value and maximum value. The description of the classified index employed the case number and percentage of the cases.  Descriptive statistics were conducted on the completion of the study. The comparison among groups was conducted on the demographic and baseline characteristics to analyze the equilibrium between groups.  Analysis of the main outcome measures: the main efficacy index will use the test of superiority. In addition, the dereasee value os DBP of each subject after treatment of 8 weeks will also be calculated, and descriptions in each group were done (mean, standard deviation, median, minimum, maximum). Comparisons between groups used analysis of variance considering center effect.  Analysis of the secondary outcome indicators: the center effect was not considered in principle. Comparisons between groups employed the variance analysis, chi-square test or nonparametric statistical method.  Analysis of the safety evaluation: parameters of safety evaluation included adverse events/ adverse drug reaction (ADR)/important adverse events or serious adverse events, physical examination and laboratory examination and a 12-lead electrocardiogram. Detailed description was conducted on the cases of adverse events during the test. The incidence rates of the adverse events between the two groups were summarized and compared. The indexes of laboratory examination were statistically described. The difference between two groups was compared when it was necessary. A detailed description of the laboratory indexes and normal cases before treatments was conducted.  This study did not conduct interim analysis. |

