**Results**

**Effective results:**

This study selected a total of 401 cases of patients with mild to moderate primary hypertension. After cleaning for 2 weeks, 283 subjects were randomly enrolled into groups, of whom there were 34 cases of dropping (12%) 7 cases were excluded (2.5%). The full analysis set included 279 cases (Allisartan Isoproxil with doses of 80, 160, 240mg and losartan of 50mg included 69, 68, 72, and 70 cases). The PPS included 246 cases (Allisartan Isoproxil with doses of 80, 160, 240mg and losartan of 50mg included were 60, 58, 67, 61 cases).

In FAS analysis, the sitting blood pressure (systolic/diastolic blood pressure) of the subjects treated with Allisartan Isoproxil of 80, 160, 240mg and losartan of 50mg for 4 weeks was 11.33/6.96, 11.35/6.35, 10.85/8.39, mmHg and 11.41/7.67mmHg less than that of the relative baseline. The sitting blood pressure (systolic/diastolic blood pressure) in various groups treated for 8 weeks was 9.12/6.30, 11.04/7.22, 11.76/8.57mmHg and 12.39/8.41mmHg was less than that of the relative baseline. The absolute decreasing value of the blood pressure increased with the increasing dose of Allisartan Isoproxil . The absolute decreasing value of the Allisartan Isoproxil (240 mg) was similar to that of the Losartan (50 mg), but there were no significant difference between groups.

After the treatment with Allisartan Isoproxil 80, 160, 240 mg and losartan of 50mg for 4 weeks, the percentrate of the standard meeting of the sitting blood pressure were 57.97%, 42.65%, 59.72% and 52.86%. The average decreasing values of the sitting blood pressure were decreased by 14.15/9.40, 15.17/11.41, 14.07/11.74mmHg and 18.57/12.84mmHg comparing with that of the baseline, but there was no significant difference between groups. After 8 weeks of treatment, compliance percentages of the sitting blood pressure were 43.48%, 52.94%, 58.33% and 54.29%, which were dropped by an average of 18.63/12.33, 20.06/13.22, 17.69/13.02 mmHg and 19.39/14.11mmHg comparing with that of the baseline, but there were no significant differences between groups.

90.32% of the subjects were mild hypertension. After treatment for 8 weeks with Allisartan Isoproxil with concentrations of 80, 160, 240mg and losartan of 50mg, the average sitting blood pressures were decreased by 8.18/5.84, 11.14/7.71, 12.48/8.82 and 12.22/7.89 mmHg comparing with that of the baseline.

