## Secondary objective

The secondary objective was to compare the following aspects of primary hypertensive patients at low-medium risk treated with 240 mg Allisartan Isoproxi tablet (ALS-3) and placebo:

- The change of trough mean seated DBP after 4 weeks treatment;
- The change of trough mean seated SBP after 4 ,8weeks treatment;
- Effective rate after 4,8 weeks treatment (Seated position SBP/DBP＜140mmHg/85mmHg, or SBP decreasing of 20 mm Hg and/or DBP decreasing 10 mm Hg);
- The change of trough mean seated SBP/DBP after 4 ,8weeks treatment in effective patient;
- Safety evaluation after 8 weeks.

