## Statistical methods

### Aalysis method

Statistical analysis using SAS9.13 statistical analysis software for calculation. Quantitative description of the calculation of mean and standard deviation, median, minimum value, maximum value. Classification index described by number and percentage of cases.

Completion of the study will be carried out descriptive statistics on the demographics and baseline characteristics were compared between the two groups in a balanced analysis between groups.

Analysis of the main outcome measures: the main efficacy index will adopt non inferiority test. In addition, also calculate each subject after 8 weeks of treatment, DBP decreased and the seat value groups (mean standard deviation, median, minimum and maximum), groups were compared using analysis of variance center effect considered.

Analysis of secondary efficacy indicators: in principle does not consider the center effect, by using variance analysis, chi square test or nonparametric statistical method for comparison between groups.

Analysis of safety evaluation, safety evaluation included adverse events / ADR / important adverse events or serious adverse events, physical examination and laboratory examination and a 12 lead electrocardiogram. Cases of adverse events during the detailed description of test, summary comparison of incidence of adverse events between the two groups. Statistical description and index of laboratory examination and necessary changes were compared between the two groups. A detailed description of laboratory indexes was normal before treatment after treatment of abnormal.

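### The secondary comparison of blood pressure change among 'effective' patients selects on the outcome itself, so it is not a randomised comparison and understates the drug effect

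*Protocol*

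**What the plan says.** The endpoint "The change of trough mean seated SBP/DBP after 4, 8weeks treatment in effective patient" stands in section 8.2 (Secondary outcome) and, in near-identical words, in section 2.2 and in the objective and outcome rows of the Protocol summary.

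The note in section 8.2 says who is effective: "Effective respond was defined as the seated SBP/DBP<140/85mmHg, or seated SBP decrease≥20mmHg and/or seated DBP≥10mmHg". The last criterion lacks the word for a decrease, but section 2.2 makes clear that a diastolic fall is meant.

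Section 2.2 frames every item on its list as a comparison; the objective is "to compare the following aspects of primary hypertensive patients at low-medium risk treated with 240 mg Allisartan Isoproxi tablet (ALS-3) and placebo". Section 11.4.1 analyses secondary indicators "by using variance analysis, chi square test or nonparametric statistical method for comparison between groups". Section 11.3 applies a two-sided threshold of P ≤ 0.05 to all tests other than the primary one. Nothing in the protocol marks the effective-patient item as descriptive or allows for the selection.

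**The concern.** Randomisation makes the two arms comparable when everyone randomised is compared. Here the group is formed afterwards, by the outcome. A drug that works brings extra patients over the response threshold, many of them only just over it, and these marginal responders hold down the active arm's responder mean. The placebo responders are fewer and are a differently selected part of their arm. The difference in means between the two groups mixes the drug effect with this difference in selection.

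At stake is one listed efficacy result. A real effect would look small and would probably be non-significant. A reader could conclude that the drug adds little in patients who respond, when the design cannot answer that question.

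**Working it through.** **1. The plan's own figure.** Inputs from the Protocol summary and section 11.1: "bilateral α = 0.05", "and the standard deviation SD = 7.8 mmHg", a difference of 3 mmHg and 108 per arm.
- Standard error = 7.8 × √(2/108) = 1.061, and 3/1.061 = 2.826.
- Power is 0.807 by the normal formula and 0.803 by the noncentral t with 214 degrees of freedom. The protocol prints 0.80229.
- n = 2 × (1.96 + 0.842)² × 7.8² / 3² = 106.1, so 107 per arm against the stated 108.

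The sample size for the primary endpoint is sound. The protocol gives no figure for the effective-patient endpoint.

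**2. Simplest case: response means a diastolic fall of at least 10 mmHg.** For a normal fall with mean μ and SD σ, the mean among responders is μ + σφ(k)/(1 − Φ(k)), with k = (10 − μ)/σ. The protocol gives no placebo fall, so 3 and 6 mmHg are assumed. The drug adds 3 mmHg in every patient.
- Placebo μ = 3: k = 0.897, mean = 3 + 7.8 × 0.2667/0.1847 = 14.26. Active μ = 6: k = 0.513, mean = 6 + 7.8 × 0.3498/0.3040 = 14.97. Difference 0.71.
- Placebo μ = 6: mean 14.97. Active μ = 9: k = 0.128, mean = 9 + 7.8 × 0.3957/0.4490 = 15.87. Difference 0.90.

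A uniform 3 mmHg effect shows as 0.7 to 0.9 mmHg.

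**3. Full response rule, by simulation (one million patients per arm).** From the protocol: diastolic SD 7.8, effect 3. Assumed: systolic SD 12, correlation 0.6, baseline 150 (SD 8) / 96 (SD 4) held within the entry limits, and the placebo falls and systolic effects below. Power is for the diastolic comparison among the responders expected from 108 per arm.

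| Placebo fall (SBP/DBP) | SBP effect | Responders, placebo v active | Responder-only DBP difference | Responder-only SBP difference | Power, DBP |
|---|---|---|---|---|---|
| 4/3 | 5 | 24% v 38% | 0.70 | 2.4 | 9% |
| 4/3 | 4 | 24% v 37% | 0.94 | 1.4 | 12% |
| 6/5 | 5 | 32% v 48% | 0.86 | 2.6 | 12% |
| 6/5 | 4 | 32% v 47% | 1.05 | 1.6 | 16% |
| 8/6 | 5 | 37% v 54% | 0.97 | 2.6 | 15% |
| 8/6 | 4 | 37% v 53% | 1.12 | 1.6 | 18% |

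With every baseline fixed at 150/97, the diastolic difference is 0.7 to 1.1 mmHg and power 8 to 17%. Varying the systolic SD from 11 to 13 and the correlation from 0.4 to 0.7, at a systolic effect of 5, gives 0.6 to 1.1 mmHg and 7 to 17%.

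**4. When the sign changes.** With a true systolic effect of 0, the responder-only systolic difference is about −2.4 to −3.0 mmHg, in favour of placebo. At a systolic effect of 2 it is −0.3 to −0.7. At 3 (placebo fall 6/5.57) it is +0.7. The diastolic difference stayed positive in every scenario. With no effect on either pressure, the responder means agree (13.22 v 13.22).

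**5. The earlier phase II trial (section 1.2).** The protocol reports week-8 falls in responders for 80, 160 and 240 mg and losartan, "which were dropped by an average of 18.63/12.33, 20.06/13.22, 17.69/13.02 mmHg and 19.39/14.11mmHg". Responders at week 8: 58.33% of 72 = 42 on 240 mg, and 43.48% of 69 = 30 on 80 mg.

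| 240 mg minus 80 mg | All FAS patients | Responders only |
|---|---|---|
| Week 8 SBP | 11.76 − 9.12 = +2.64 | 17.69 − 18.63 = −0.94 |
| Week 8 DBP | 8.57 − 6.30 = +2.27 | 13.02 − 12.33 = +0.69 |
| Week 4 SBP | 10.85 − 11.33 = −0.48 | 14.07 − 14.15 = −0.08 |
| Week 4 DBP | 8.39 − 6.96 = +1.43 | 11.74 − 9.40 = +2.34 |

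If the responder systolic SD is 8 to 12 (assumed), the standard error of the −0.94 is SD × √(1/42 + 1/30) = 1.9 to 2.9 mmHg.

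**The case against.** A reader might infer three stronger points, and the documents support none of them.
- **That the analysis will reverse the drug effect.** Under plausible inputs the active arm stays ahead on both pressures. A wrong sign needs a drug that lowers diastolic but hardly systolic pressure.
- **That the sponsor's own data show the reversal.** The week-8 systolic figure of −0.94 lies well within its standard error, and the protocol reports no significant difference between groups. At the same visit diastolic pressure does not reverse, and at week 4 the diastolic gap widens. These are also active doses, not drug against placebo. The figures illustrate the problem but do not prove it.
- **That the endpoint supports the efficacy claim.** Sections 2.1 and 11.3 rest superiority on week-8 diastolic pressure alone. If the drug had no effect on either pressure, the selection would create no false signal.

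It is also fair to say that section 11.4.1 offers only a general menu of methods, so the P ≤ 0.05 test of this item is read from sections 2.2, 11.3 and 11.4.1 together. The sound comparisons are already listed: the effective rate and the all-patient mean changes.

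These points limit the consequence and leave the defect standing. The text calls the item a comparison and makes no exception for it. The choice of endpoint is fixed in the protocol and is not a detail left to an analysis plan.

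**Conclusion.** The point holds for one secondary endpoint. The responder-only contrast is not a randomised comparison and does not estimate the treatment effect. If the drug shifts every patient by the planned 3 mmHg diastolic, it shows about 0.7 to 1.1 mmHg, with power of about 8 to 18% at 108 per arm. These ranges rest on the protocol's SD of 7.8 and on the assumed placebo falls, systolic inputs, correlation and baselines; other values move the figures, but the diastolic shrinkage appeared in every scenario run. The selection argument itself needs no assumed numbers: membership depends on the outcome and differs by arm whenever the drug changes the response rate.

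**What to change.** Take the effective-patient item out of the between-group comparisons in sections 2.2 and 8.2 and in the matching Protocol summary rows. Alternatively, keep it and add that it is descriptive by arm with no between-group test. Leave the effective rate and the mean changes in the full analysis set as the secondary randomised comparisons. While editing, bring the diastolic criterion in the section 8.2 note into line with section 2.2, so that it reads as a decrease.

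The cost is wording only. No data, visits or patients are added, and the one test lost could not be interpreted.
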